**Instructions:** The purpose of this research protocol is to provide IRB members and reviewers with sufficient information to conduct a substantive review. If a separate sponsor’s protocol exists, please submit it in addition to this document.

Complete all of the sections below.  For more detailed instructions, please consult the Investigator’s Manual or IRB website (links provided below).

| **General Information** | |
| --- | --- |
| **Protocol #** (if assigned): | |
| **Version Date:** 21 April 2015 | **Version Number: Version # 1** |
| **Principal Investigator:** [name] | |
| **Faculty Advisor (**if PI is a student**):** | |
| **Protocol Title:** Evaluating the Impact of School-based Health Programs on Children’s Well-being and Academic Performance | |

1. **Specific Aims**

The overall objective of the proposed research project is to determine whether children’s health and academic performance can be improved by a school-based health program currently piloted by a local NGO called *Angels of Mercy* in Lusaka, Zambia. The school health program has two components: the training of selected teachers to become “School Health Workers”, and bi-annual health screenings of all students.

In the proposed study, we hope to collect data on primary school students in Lusaka to address the following four specific aims:

1) Establish the prevalence of acute and chronic infections among primary school students in Lusaka.

2) Evaluate the impact of the school-based health programs (SBHP) on the prevalence of acute and chronic diseases among school going children.
3)Evaluate the impact of SBHP on school attendance and academic achievement.
4)Evaluate the impact of the School Health Worker training on teachers motivation and general school perceptions of school administrators, children and their mothers.

1. **Background**

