According to the latest data from the World Bank and UNICEF, primary school enrollment in Zambia was 94% in 2012 and school attendance was over 81% between 2008 and 2012.1,2 The main sources of primary schooling in Zambia are government schools, private schools and community schools. Government schools are intended to be free for Zambians until grade 7, but they are not accessible by all: some charge fees for uniforms and other school supplies or are located in areas that make them inaccessible to some of the population.3 Community schools attempt to fill this gap by providing locally managed primary education to those in need. The quality of community schools, however, is inconsistent.4
School-based health screenings are a proven cost-effective method to manage preventable, treatable illnesses and improve school attendance in developing countries.5-8 Although the World Health Organization (WHO) recommends that all children in areas with high risk for helminth infection are treated with deworming medications, study results on the effectiveness of these interventions have been inconsistent. A study by Clarke et al. (2008) in western Kenya found that students in schools randomized to receive an intervention providing intermittent preventative treatment showed significant improvements in anemia, hemoglobin concentration, and sustained attention.7 Also in Kenya, Miguel and Kremer (2004) found that children in schools randomly assigned to a deworming intervention showed a one-quarter decrease in school absenteeism along with significant improvements in prevalence of hookworm, roundworm, schistosomiasis, and whipworm; self-reported health; and height for age.­8 A meta-analysis by Taylor-Robinson et al. (2012) found mixed results regarding the effects of deworming medications in children aged 16 and younger. Screening children for worms and then treating those who were infected appeared to increase weight and hemoglobin, but showed an unclear effect on cognitive functioning; single and multiple doses of deworming for all children without screening first, however, showed little effect on weight, hemoglobin, cognitive function, and school attendance.These results were not modified when stratified according to prevalence of helminth endemic in the area.9

*The new School Health Worker Program in Zambia*

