**2.2 Describe the significance of the research, and how it will add to existing knowledge**

While free health care is provided for children under five years of age in Zambia, research on the health and well-being of the school-aged population in Zambia is limited. The newly designed SBHP currently piloted in 7 schools in Lusaka offer a potentially effective way to improve the health of students in Lusaka and elsewhere in the country; the aim of this project is to assess the effectiveness of these programs.

In our literature review, we could not identify any other program that utilizes a model similar to the SBHP program; for this reason among others, understanding if this innovative program is achieving its intended purpose is particularly important.

While improving population health through schools has long been a focus of the Zambian Ministry of Education, the SBHP model represents a new approach. School is an appropriate setting for a health intervention in Zambia because school-aged children are the population most affected by infectious diseases, and primary school attendance is as high as 94%.1 Additionally, no other known program utilizes a model similar to HK/BF’s SHW program in which teachers may make referrals to health centers. One program conducted by the Zambian Ministry of Education focused on strengthening teachers’ “professional skills” with in-service teacher trainings and follow-up “professional support”.11 While this program did work on developing leadership skills, it did not emphasize teacher empowerment, a point of the SHW program. Other school-based health interventions in Zambia focus mainly on health curriculum, such as the Nutrition Education in Basic Schools (NEBS) project also led by the Zambian Ministry of Education.10 Teachers in these other programs were also not trained to perform first aid or make referrals.

1. **Study Setting**
   1. **Identify the sites or locations where the research will be conducted.**

This study will be conducted in 14 primary schools in Lusaka district, Zambia.

- 1. **Describe the Principal Investigator’s experience conducting research at study site(s) and familiarity with local culture**The PI has extensive experience in Zambia. He has been conducting research there since 2009, and has established a close working relationship with partners at the University of Zambia as well as the Ministries of Education and Healthth.
  2. **Is the research conducted outside the United States?**

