Fourteen community schools will be involved in the study. In each school, three grades will be selected for the study; in treatment schools, two grades will be randomly selected among those directly taught by SHWs; the grades in the control group will be chosen to match the ones in the treatment group. To be able to link health status directly to standardized tests, all students in grade 7 will be invited to participate in the study in the 14 schools. Intervention schools will receive the SHW Program as well as baseline, midline, and endline health screenings. For each of the seven schools, we will identify a control school within Lusaka district. Control schools will be chosen based on the overall school size, number of pupils in each grade, and average test score performance.

*Outcome measures*
The primary outcome of the study will be child health (prevalence of acute and chronic infection at endline) as well as academic performance (school attendance and grade performance).

The quantitative assessments at baseline, midline and endline will be complemented by qualitative work. For the qualitative component, we will employ a non-probabilistic, stratified purposeful sampling methodology. In our study we will capture the opinions of SHWs, school administrators, mothers and children from a sample of community schools with the SHW program. We will use a mixture of qualitative research methods, namely semi-structured individual interviews and focus group discussions (FGDs).

We will sample a total of 10 SHWs across the seven intervention schools. Of the schools selected, we will randomly sample 3 schools for additional investigation. From this pool of 3 schools we will conduct individual interviews with the school administrators (preferably the headmaster), and FGDs with mothers and children. There will be a total of 3 administrator interviews (1 per school) and 7 FGDs with mothers and children (1 per intervention school).

*Internal validity*

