2. Bi-annual school based preventive health screening days. In collaboration with the Ministry of Health bi-annual health screening days will be conducted at all target community schools. All health screenings will be conducted by nurses and clinical officers from the local government health clinic and supported by trained SHWs. Parents or guardians are expected to attend screening days with their children and informed consent is required by both the child and guardian. As part of the screening, a complete physical examination is performed including urine screening for schistosomiasis, which is endemic in the region. All children receive a dose of vitamin A, mebendazole for presumptive deworming, and, if indicated, Praziquantil for schistosomiasis. Medication for simple acute ailments will be dispensed to the guardian of sick pupils upon the completion of the health screening. All students with chronic or severe ailments will be referred to the local health centre. AoM offers health screenings to all students within a class and are not limited to the students whom will participate in the study.
*Control group:* 7 schools will be used as the control group. All control schools will complete a baseline survey including height/weight, mid upper-arm circumference, and self-reported health at baseline, as well as an endline survey including a complete health screening.

- 1. **Does the study involve the collection of data/specimens (including the use of existing data/specimens)?**

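### Aim 1 names primary pupils in Lusaka as its target population, but the design samples selected grades in 14 non-randomly chosen community schools, so it can support only a narrower prevalence claim

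*Protocol*

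**What the plan says.** Section 1 (Specific Aims) sets as the first aim: "Establish the prevalence of acute and chronic infections among primary school students in Lusaka". It gives no qualification by school type, grade or area.

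Section 2.1, on primary schooling, states: "The main sources of primary schooling in Zambia are government schools, private schools and community schools". Of the last group it says: "Community schools attempt to fill this gap by providing locally managed primary education to those in need".

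The Sampling text under Study Design says: "Fourteen community schools will be involved in the study". Section 2.2 identifies the programme: "The newly designed SBHP currently piloted in 7 schools in Lusaka". For the other seven, the Sampling text says: "Control schools will be chosen based on the overall school size, number of pupils in each grade, and average test score performance". Three grades are used per school. Grade 7 is always in. In treatment schools, "two grades will be randomly selected among those directly taught by SHWs", and the control grades are chosen to match. Under Recruitment Methods, only pupils who return a parental consent form are enrolled.

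On measurement, the Sampling text gives intervention schools health screenings at baseline, midline and endline. The Control group paragraph says: "All control schools will complete a baseline survey including height/weight, mid upper-arm circumference, and self-reported health at baseline". It places a complete health screening in those schools at endline.

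**The concern.** An aim to establish a prevalence names a population, and the sample has to reach that population or be tied to it by a frame or weights. Here the sample comes from one of the three school sectors that the protocol itself lists, and that sector is described as serving children whom the others do not reach. Within it, schools enter because they run the programme or resemble those that do, and grades enter partly because of who teaches them. These choices serve the comparison between groups but do not make the sample represent Lusaka.

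Aim 1 also does not say which screening round supplies the prevalence. The two halves of the sample are clinically screened for the first time about a year apart.

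At stake is a mislabelled descriptive result. Section 2.2 says research on this age group in Zambia is limited, and results are to be shared with school boards and two ministries. A figure labelled as Lusaka's could be read as city-wide.

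**Working it through.** **1. The protocol's own sample size.** About 80 pupils per school (Internal validity text) × 14 schools = 1120, which matches the total in the Data/Statistical Analyses Plan. That figure was set for the comparison of groups (0.50 against 0.35, design effect 2, 10% attrition). It has no bearing on whether Aim 1 is representative.

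**2. Target against sample, level by level.**

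| Level | Aim 1 | Design |
| --- | --- | --- |
| Sector | all primary schooling in Lusaka | community schools only |
| Schools | all | 7 programme schools and 7 matched to them; no probability draw |
| Grades | all primary grades | grade 7, plus 2 drawn at random among SHW-taught grades or matched to these |
| Pupils | all | those enrolled with consent |

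Nothing in the protocol links the right-hand column to the left.

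**3. Which clinical infection data exist, and when.**

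- Intervention schools: baseline, midline and endline. At baseline this is 7 × 80 = 560 of 1120 pupils, or 50%.
- Control schools: anthropometry and self-reported health at baseline, then a complete screening at endline. With 10% attrition that is 560 × 0.9 = 504 pupils, who have not had the programme.

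**4. Precision of what can be estimated.** Inputs from the protocol: p = 0.50 (expected baseline) and design effect 2. Half-width = multiplier × √(p(1 − p) × 2 / n).

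- Baseline, intervention schools, n = 560: √(0.25 × 2/560) = 0.0299. Normal: 1.96 × 0.0299 = 0.059. With t on 6 df: 2.447 × 0.0299 = 0.073.
- Endline, control schools, n = 504: √(0.25 × 2/504) = 0.0315. Normal: 1.96 × 0.0315 = 0.062. With t on 6 df: 2.447 × 0.0315 = 0.077.

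These half-widths describe the sampled schools and grades. They say nothing about the rest of the city.

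**5. Distance from a city-wide figure.** Let s be the community schools' share of Lusaka's primary pupils. Then sample prevalence − city prevalence = (1 − s) × (p_community − p_other), even if the 14 schools represented their own sector perfectly. The protocol gives neither s nor p_other. As pure assumptions, take p_community = 0.50, s from 0.1 to 0.5 and p_other from 0.30 to 0.70. The extremes are 0.9 × (0.50 − 0.30) = +18 points and 0.9 × (0.50 − 0.70) = −18 points, and the difference is zero when p_other = 0.50. The spread shows only that size and sign are undetermined. It is not an estimate of bias, and enrolling more pupils in the same schools would not reduce the difference.

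**The case against.** The strongest defence is that the phrase gives a location. The sentence introducing the aims uses nearly the same words for the pupils on whom data will be collected. The Sampling text is open about community schools and three grades, and no Lusaka-wide estimator is described. That reading is possible. It does not remove the problem, because the aim still names a population whose prevalence is to be established and nothing restricts it. It does limit the seriousness: this is the wording of a descriptive aim, and the overall objective and the power statement concern programme effects.

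Several stronger readings are tempting but are not supported:

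- *The schools and grades were hand-picked.* Control schools follow stated matching criteria, and two grades per treatment school are drawn at random, though only among SHW-taught grades. The accurate description is non-probability selection.
- *Programme-free infection data come only from the intervention schools.* Control pupils are fully screened at endline without having had the programme. What holds is narrower: baseline clinical screening is listed for seven schools only.
- *The prevalence will be wrong by a known number of points.* Any such figure rests wholly on assumed shares and prevalences.
- *Clustering will be ignored, or treated and untreated endline data pooled.* The Data/Statistical Analyses Plan clusters all standard errors by school, and the protocol never proposes such pooling.

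One wording could suggest wider baseline screening. The screening days are to be held at all target community schools, and the exclusion criteria use the term target for all 14. However, those days are described as a component of the intervention, and the Control group paragraph does not list them.

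**Conclusion.** The point stands in a limited form. Aim 1 claims a population that the design does not sample, and followed as written it would give a prevalence with the wrong label. The conclusion rests on the protocol's own description of school types, school and grade selection, and screening schedule, and it needs no outside figure. A later analysis plan could not cure it by method alone, because no government or private school is in the study.

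How far the sample prevalence lies from the city's, and in which direction, cannot be derived from the documents. A reader might infer that the trial is bound to overstate infection because community schools serve children in need. The protocol gives no prevalence by school type to support that.

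The quantity that can be estimated has a half-width of about ±5.9 points (normal) or ±7.3 points (t, 6 df) at baseline in the seven intervention schools. This assumes 560 pupils, 50% prevalence and design effect 2. The comparisons under Aims 2 and 3 are not touched by this point. The change should be made but is not critical.

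**What to change.** Restate Aim 1, for example: *estimate the prevalence of acute and chronic infection among enrolled pupils in the selected grades of the participating Lusaka community schools.* Then:

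- Name the data source: the baseline screening in the seven intervention schools. Report the endline screening in the seven control schools separately, as programme-free prevalence about a year later.
- Call the first figure baseline prevalence. Before calling it pre-programme, confirm that these pupils had no earlier exposure. Section 2.2 describes the programme as already being piloted in seven schools, while the Study Design text places baseline before rollout.
- Use the school-clustered standard errors already planned. With seven schools per figure, the t interval on 6 df is the more cautious choice.
- Do not present either figure as prevalence for Lusaka.

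The cost is rewording one aim and how it is reported, and a narrower descriptive claim. Sample size, data collection and Aims 2 and 3 are unchanged. A true city-wide prevalence would need a separate probability sample across school types, which this study does not plan.

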**2.1 Provide the scientific background and rationale for the study**

While a lot of local and international efforts have focused on improving the health of children under the age of five in Zambia in recent years, relatively little is known regarding children’s wellbeing in late childhood. Two recent pilot studies suggest that children in this age group are suffering from a heavy exposure to both infectious and chronic health problems, which do not only undermine their physical development, but also limit their ability to attend school and excel as students. In this study, we propose to evaluate the effectiveness and impact of a new school-based health program (SBHP), which consists of two school-based interventions designed to improve children’s health:

1) *Bi-annual school health screenings*: Trained health workers (nurses trained by the government) come to schools every six months to i) provide children with vitamin A supplementation and deworming medication, ii) perform anthropometric measurements, and iii)test and examine children for the following conditions: schistosomiasis, acute respiratory infections, fungal infections, diarrheal diseases, malaria, tuberculosis, urinary tract infections, eye infections, and other acute and chronic conditions observed by the clinician during the physical examination.

2) A newly developed *School Health Worker program*: For the school health worker program, teachers are trained for 100 hours on the recognition of acute and chronic infections as well how to design and implement health education curricula, improve school water, sanitation and hygiene conditions (WASH), and provide basic first aid care such as management of trauma and bleeding, preparation of ORS, and pre-referral management. School administrators are trained for 45 hours on how to supervise, manage, and motivate school health workers, design school-wide health education curricula, and improve school WASH conditions.

*Background: Primary Schooling and Health Screenings*

According to the latest data from the World Bank and UNICEF, primary school enrollment in Zambia was 94% in 2012 and school attendance was over 81% between 2008 and 2012.1,2 The main sources of primary schooling in Zambia are government schools, private schools and community schools. Government schools are intended to be free for Zambians until grade 7, but they are not accessible by all: some charge fees for uniforms and other school supplies or are located in areas that make them inaccessible to some of the population.3 Community schools attempt to fill this gap by providing locally managed primary education to those in need. The quality of community schools, however, is inconsistent.4
School-based health screenings are a proven cost-effective method to manage preventable, treatable illnesses and improve school attendance in developing countries.5-8 Although the World Health Organization (WHO) recommends that all children in areas with high risk for helminth infection are treated with deworming medications, study results on the effectiveness of these interventions have been inconsistent. A study by Clarke et al. (2008) in western Kenya found that students in schools randomized to receive an intervention providing intermittent preventative treatment showed significant improvements in anemia, hemoglobin concentration, and sustained attention.7 Also in Kenya, Miguel and Kremer (2004) found that children in schools randomly assigned to a deworming intervention showed a one-quarter decrease in school absenteeism along with significant improvements in prevalence of hookworm, roundworm, schistosomiasis, and whipworm; self-reported health; and height for age.­8 A meta-analysis by Taylor-Robinson et al. (2012) found mixed results regarding the effects of deworming medications in children aged 16 and younger. Screening children for worms and then treating those who were infected appeared to increase weight and hemoglobin, but showed an unclear effect on cognitive functioning; single and multiple doses of deworming for all children without screening first, however, showed little effect on weight, hemoglobin, cognitive function, and school attendance.These results were not modified when stratified according to prevalence of helminth endemic in the area.9

*The new School Health Worker Program in Zambia*

In response to Zambia’s context and the health needs of young people, Healthy Kids/Brighter Future (HK/BF), an international NGO, in conjunction with Angels of Mercy (AoM), a registered Zambian NGO, and the Ng’ombe government health centre have recently developed a School Health Worker (SHW) program and piloted it in the Ng’ombe area. The SHW program is based on Zambia’s national Community Health Worker (CHW) model. The program’s purpose is to address issues of health system access and health education, with the broad goal of reducing the burden of preventable diseases that disproportionately affect children and young adults, including HIV/AIDS, diarrheal diseases, and nutritional deficiencies. The SHW program takes an innovative approach, working with school administration and training and empowering select teachers to conduct health lessons, perform first aid, and identify sick children that might require referral. The primary goal of this program is for SHWs to improve the health of young people through providing regular health education lessons and identifying negative health conditions in children in a timely manner and to ensure that the children receive prompt care. The SHW program also aims to empower the teachers who are trained to be SHWs.

To date, school-based health interventions in Zambia have focused mainly on health education.10 Between 2005-2009, USAID funded the Community Health and Nutrition, Gender and Education Program (CHANGES2) program supporting the Zambian Ministry of Education’s activities in four provinces, including Lusaka.11 CHANGES2 focused on strengthening teachers’ “professional skills,” as well as health education, particularly HIV/AIDS prevention. While it sought to expand schools’ health services, it did not employ teachers as health workers in schools.

